### Primary analysis

DUP and referral rates for intervention area compared to the control area will be monitored and evaluated every three months throughout implementation and at the culmination of the intervention (2 year period). In the TIPS study, despite DUP being relatively short in both areas (with a combined median of 10 weeks), DUP was significantly reduced in the intervention area, reduced to a median of 5 weeks compared with 16 weeks in the control area [31]. In this proof-of-principle trial, we make no a priori assumptions about effect size since the methodology and setting is unique. The key outcome of this trial will be an estimate of the effect size, which will inform a definitive trial. The confidence intervals for different levels of increase in the number of new referrals in the target area are shown in Table 3.

**Table 3 T3:** Confidence Intervals for the target area based on predicted increase in referral rate

**Yearly referral rate increase**	***Predicted *****confidence Interval (+/−)**	**CI width**
30	218	90-526
40	187	121-495
50	166	142-474
**60**	**151**	**157-459**
70	139	169-447
80	130	178-438
90	123	185-431
100	116	192-424

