**Methods/Design:**

A quasi-experimental trial, comparing a targeted intervention area with a ‘detection as usual’ area in the same city. A proof-of–principle trial, no a priori assumptions are made regarding effect size; key outcome will be an estimate of the potential effect size for a definitive trial. DUP and number of new cases will be collected over an 18-month period in target and control areas and compared; historical data on DUP collected in both areas over the previous three years, will serve as a benchmark. The intervention will focus on reducing two significant DUP component delays within the overall care pathway: delays within the mental health service and help-seeking delay.

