## Methods

### Design

This is a quasi-experimental, proof-of-principle prospective trial comparing an intervention area in the south of the city, to the non-intervention remainder of the city.

Incident cases of first episode psychosis from these areas will be determined and their DUP and care pathways ascertained over the following 18 months. We also benefit from recent historical DUP data (National EDEN) [19] for both target and control areas.

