### Sampling

Birmingham is served by a single mental health service, which served as the ‘blueprint’ for the Government’s National Service Framework for Mental Health [21]; it has a number of community services including Home Treatment and Assertive Outreach teams, including well-developed early intervention services for first episode psychosis which were the forerunner of such services across England. It is the second most populous city in Britain with a high degree of cultural and religious diversity and is ranked third most deprived core city in England [22]. Population and ethnic profile of the intervention and control areas [23], together with the number of new cases in the previous 12 months, is shown in Table 1.

**Table 1 T1:** Socio-demographic profile of intervention and control areas

	**Population**	**Ethnic profile**
**Intervention Area**	308,150	85% White British
		8% Asian
		3% Black
**Control Area**	632, 427	62% White British
		26% Asian
		8% Black

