### Ethical approval

The trial is sponsored by Research and Innovation department at Birmingham & Solihull Mental Health Foundation Trust. Advice was sought from the National Research Ethics Service for the NHS. This public health trial falls outside of the requirements for formal approval as: no consent or recruitment of service users is required; no identifiable data will be specifically collected or used for evaluation; and the only data to be used will be anonymised DUP data and number of incident cases, both of which are routinely collected for all clients entering the specialist Early Intervention Service (for first episode psychosis) as part of their initial assessment.

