### Secondary outcome

#### Referral rates

We also predict an *increase* in referrals of young people diagnosed with a psychotic disorder from the intervention area into EIS.

Table 2 shows baseline DUP and component delays for incident cases in between August 2011 and August 2012.

**Table 2 T2:** Number of incident cases and their DUP: August 2011 – August 2012

	**New cases**	**DUP (mean; median; sd)**	**Delay in help-seeking (mean; median; sd)**	**Delay within mental health services (mean; median; sd)**	**Delay in accessing EIS (mean; median; sd)**
**Intervention Area**	88	293; 38 (867.1)	50; 0 (131.6)	211; 30 (481.4)	443; 56 (930)
**Control Area**	250	264; 58 (539)	114; 3 (271.4)113	213; 22 (511.9)	323; 105 (560.8)

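### The primary comparison is of area levels during the campaign, and the two-area historical DUP is never tied to the effect estimate, so standing area differences can enter it

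*Protocol article*

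**What the plan says.** The Design section states: "This is a quasi-experimental, proof-of-principle prospective trial comparing an intervention area in the south of the city"; the comparator is the rest of the city. The Primary analysis section sets the contrast: "DUP and referral rates for intervention area compared to the control area will be monitored and evaluated every three months throughout implementation", with a further evaluation at the end. The Abstract agrees: DUP and new cases are collected over 18 months in both areas and compared.

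Earlier data appear in two places. The Abstract says "historical data on DUP collected in both areas over the previous three years, will serve as a benchmark". The Design section says "We also benefit from recent historical DUP data (National EDEN) [19] for both target and control areas". Neither says how these data enter the effect estimate. The subsection on UK benchmark DUP data, under Secondary analysis, lists only sites outside Birmingham.

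The hypotheses concern change: a reduction in DUP (Hypothesis; Primary outcome) and a rise in referrals from the intervention area (Secondary outcome). The key output is an effect size to inform a definitive trial.

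Table 1 gives the intervention area as "85% White British" and the control area as "62% White British". Table 2, introduced as baseline, is captioned "Number of incident cases and their DUP: August 2011 – August 2012". The intervention section dates the campaign launch to January 2012.

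**The concern.** The hypotheses are about change, but the stated primary contrast is a difference in level. With one area per arm and no randomisation, a difference in level is the campaign effect plus whatever separated the areas beforehand. More cases reduce sampling error but leave that second part untouched.

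There is good reason to expect a second part. The ethnic mix differs clearly, and the Background itself links religion and culture to help-seeking. The crude case rate differs as well. Because the trial's main product is an effect size for planning a definitive trial, any standing difference would pass into that trial's design. A campaign with no effect could look helpful on median or rank-based DUP and unhelpful on a between-area comparison of referral rates.

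**Working it through.** **The plan's own figures.** No figure is given for the between-area contrast. Table 3 is the only precision statement, and it concerns the target area alone: every interval is centred on 308, for example (157 + 459)/2 = 308. It therefore cannot be used to check this comparison.

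**Inputs.** Table 1 populations: 308,150 and 632,427. Table 2 new cases: 88 and 250. Table 2 DUP (mean; median; SD): 293; 38; 867.1 and 264; 58; 539. Assumed: two-sided 5% tests, and 18-month counts of 1.5 × Table 2, that is 132 and 375.

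**Case rate**
- 88/308,150 = 28.6 and 250/632,427 = 39.5 per 100,000; ratio 0.72.
- SE of the log ratio = √(1/88 + 1/250) = 0.124; 95% CI 0.57 to 0.92; exact p = 0.009.
- At the control rate the intervention area would have about 122 cases a year, 34 more than 88 (+38%).
- If the ratio persisted for 18 months with no effect: SE = √(1/132 + 1/375) = 0.101 and z = ln(0.72)/0.101 ≈ −3.2. The chance of a significantly lower rate is about 89%.

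**Mean DUP**
- Difference 293 − 264 = +29 days, longer in the intervention area.
- SE = √(867.1²/88 + 539²/250) = 98.5; 95% CI −164 to +222.
- At 18 months the SE is 80.4, and the chance of a significantly favourable result is about 1%.

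**Median DUP, log-normal illustration**
- Ratio 38/58 = 0.66; log −0.423.
- Log-SD from √(2 ln(mean/median)): 2.02 and 1.74. Log-SD from √(ln(1 + (SD/mean)²)): 1.51 and 1.28.

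| Log-SDs | SE, 132 v 375 | z | Chance of a significant result favouring intervention |
|---|---|---|---|
| 2.02, 1.74 | 0.198 | −2.14 | 57% |
| 1.51, 1.28 | 0.147 | −2.87 | 82% |

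With the first pair, the expected 95% CI for the ratio is 0.44 to 0.96, and a simulated Mann-Whitney test gives 60%. On the Table 2 counts themselves z is −1.75 or −2.35, so whether the observed gap is significant depends on the log-SD used. The Primary analysis mentions a two-year period; with counts of 2 × Table 2 the range is 70% to 91%.

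**Precision of a baseline-adjusted contrast** (log-SDs 2.02 and 1.74)
- Campaign period only: variance 2.02²/132 + 1.74²/375 = 0.0390; margin exp(1.96 × 0.198) = ×/÷1.47.
- Adding three pre-years at the Table 2 rate (264 and 750): variance 0.0390 + 0.0195 = 0.0585; margin ×/÷1.61.
- Adding one pre-year (88 and 250): variance 0.0390 + 0.0585 = 0.0976; margin ×/÷1.84.

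These margins reflect person-level variation only. Area-by-quarter variation would widen all of them.

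**The case against.** The article is condensed. The Abstract puts the comparison and the historical benchmark in the same sentence, so the full protocol may contain a baseline-adjusted model. This stands in part: it would be wrong to say that the plan uses campaign-period data only. But the article does state its primary contrast, and the benchmark has no link to it.

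Several stronger readings are tempting, and the document does not support them.

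- A reader might infer that the areas differed in DUP before the campaign. Table 2 runs to August 2012, about seven months past the launch, so part of the median gap could be campaign effect. The mean points the other way, well within sampling error. Delay within mental health services is almost equal on means (211 v 213).
- A reader might take 57% as the false-positive rate. It depends on the model: log-SD 2.02 with mean 293 implies an SD of about 2,240, against 867.1 in Table 2.
- A reader might infer a bias as large as a real effect. The only effect quoted is 5 v 16 weeks, ratio 0.31; on the log scale, 0.66 is ln(0.66)/ln(0.31) ≈ 36% of that.
- A reader might infer that the Ethical approval text ("the only data to be used will be anonymised DUP data and number of incident cases") rules out adjustment for age or ethnicity. That text explains why formal approval was not needed; it does not define the analysis dataset.
- A reader might treat +38% as the plan's referral target. The referral hypothesis is an increase from the intervention area, and the rates above use whole populations, so age structure may explain part of the 0.72.

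The design is openly quasi-experimental and proof-of-principle, and the Discussion urges caution about ethnic diversity. Neither tells the analyst how to separate area from campaign.

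**Conclusion.** The point holds in this form: the stated primary comparison is one of levels between two non-equivalent areas, and the historical two-area DUP is not connected to the effect estimate. The differences in ethnic mix and crude case rate are clear, the latter subject to its whole-population denominators and the overlapping window. A standing DUP difference is plausible, but neither its size nor its sign is established, and the article does not say whether mean or median is the primary summary.

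The 57% to 82% and 89% figures are illustrations. They assume that the Table 2 differences persist unchanged, 18-month counts of 132 and 375, two-sided 5% tests and, for DUP, log-normality. They show that the result under no effect depends on the area gap and on the summary chosen; they do not predict the trial's error rate. The matter deserves correction because it affects the primary estimate and the data for a better contrast on DUP are described as already available.

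**What to change.** Make the primary effect estimate the area-by-period interaction on log DUP, reported as a ratio of ratios: campaign-period cases against historical cases in both areas. Restrict the historical cases to those before the January 2012 launch, and do not use Table 2 as it stands as the baseline. State when the youth access pathway began. It is part of the tested combination and has no start date in the article; if it preceded the launch, pre-launch cases may already be exposed to it.

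For referrals, model case counts (Poisson or negative binomial) with a population offset and the same interaction, where pre-launch counts are available. Case numbers are routinely collected, but the article promises historical DUP only. Fit both models by quarter, so that the standard error includes area-by-quarter variation.

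The cost is a wider interval: about ×/÷1.61 instead of ×/÷1.47 if three pre-years have case numbers like Table 2, or ×/÷1.84 with one pre-year. The method relies on parallel trends and still has one area per arm, so it removes stable area differences but not all area bias. Adjustment for age and ethnicity is optional and not needed for this change.

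### Table 3 is wrong as labelled: it treats the yearly increase in referrals as the whole sample, leaves out the 88 cases a year in Table 2, and uses a mean and SD that have no stated source

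*Protocol article*

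**What the plan says.** Under Primary analysis, the protocol article declines to assume an effect ("we make no a priori assumptions about effect size since the methodology and setting is unique") and names an estimate of the effect size, to inform a definitive trial, as the key outcome. It then says: "The confidence intervals for different levels of increase in the number of new referrals in the target area are shown in Table 3". Table 3 is captioned "Confidence Intervals for the target area based on predicted increase in referral rate". Its first column, "Yearly referral rate increase", runs from 30 to 100 in tens. The second gives a predicted ± value, from 218 down to 116. The third, headed *CI width*, gives pairs from 90-526 to 192-424. The row for 60 is in bold (±151, 157-459). No confidence level, mean, SD or source is given.

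Table 2, under Referral rates, is captioned "Number of incident cases and their DUP: August 2011 – August 2012". It gives the intervention area 88 new cases with DUP mean 293, median 38 and SD 867.1, and the control area 250 new cases with mean 264, median 58 and SD 539.

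The abstract sets the window and the comparison: "DUP and number of new cases will be collected over an 18-month period in target and control areas and compared". The Design section mentions another data source: "We also benefit from recent historical DUP data (National EDEN) [19] for both target and control areas".

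**The concern.** A reader takes a row labelled as an increase of 60 a year to show the precision expected once 60 cases a year are added to those the area already produces. The half-widths shrink as though the first column were the entire sample, and the common centre of the intervals is not a mean printed anywhere in the article.

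Because no effect size is assumed, Table 3 is the only numerical statement of what the trial can deliver. Someone planning the definitive trial would read it for the precision achievable at a given referral rate. As printed, it cannot be used for that. It also describes the mean of one area, whereas the key outcome is an effect size from comparing two areas.

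**Working it through.** **Inputs.** Table 3: eight increases, half-widths and limits. Table 2: 88 and 250 cases in 12 months; SDs 867.1 and 539. Window: 18 months, from the abstract and Design (Primary analysis also mentions a 2 year period). Assumptions: two-sided 95% confidence, since no level is stated, and DUP in days, since the tables give no unit.

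**1. Reproduce the printed table.** Midpoints: (90 + 526)/2 = 308, (157 + 459)/2 = 308, (192 + 424)/2 = 308, and likewise in the other five rows.

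Taking n as the first column, the implied SD is half-width × √n / t(0.975, n−1). From row 30 to row 100 this gives 583.8, 584.7, 584.1, 584.5, 583.0, 584.2, 587.3 and 584.6. A single SD of 585 returns all eight half-widths after rounding. For example:
- n = 30: 2.045 × 585/√30 = 218
- n = 60: 2.001 × 585/√60 = 151
- n = 100: 1.984 × 585/√100 = 116

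If n is instead 88 + increase, no single SD fits: the implied value drifts from 1196 in the first row to 806 in the last. The increase was used as the sample size.

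**2. Compare the inputs with Table 2.** Neither 308 nor 585 appears there. The area means are 293 and 264, pooled (88 × 293 + 250 × 264)/338 = 272. The SDs are 867.1 and 539, pooled √[(87 × 867.1² + 249 × 539²)/336] = 640.

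**3. Recompute with n as labelled.** The 12-month n is 88 + increase and the 18-month n is 1.5 × (88 + increase). The half-width is t(0.975, n−1) × SD/√n.

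| Increase | Printed ± | n, 12 mo | SD 585 | SD 867.1 | n, 18 mo | SD 585 | SD 867.1 |
|---|---|---|---|---|---|---|---|
| 30 | 218 | 118 | 107 | 158 | 177 | 87 | 129 |
| 40 | 187 | 128 | 102 | 152 | 192 | 83 | 123 |
| 50 | 166 | 138 | 98 | 146 | 207 | 80 | 119 |
| **60** | **151** | **148** | **95** | **141** | **222** | **77** | **115** |
| 70 | 139 | 158 | 92 | 136 | 237 | 75 | 111 |
| 80 | 130 | 168 | 89 | 132 | 252 | 73 | 108 |
| 90 | 123 | 178 | 87 | 128 | 267 | 70 | 104 |
| 100 | 116 | 188 | 84 | 125 | 282 | 69 | 102 |

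With the table's own SD, every printed half-width is too wide. With Table 2's SD over 12 months, the printed values are too wide at +30 to +70 and too narrow at +80 to +100. With Table 2's SD over 18 months, they are too wide in every row.

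**4. Try the other reading.** If the column were total yearly cases, the arithmetic would hold for 12 months. The header, caption and lead-in sentence would then be wrong, and the rows for 30 to 80, including the bold one, would lie below the 88 cases already seen, although the trial predicts a rise.

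**5. Illustrate the between-area contrast.** Over 18 months the control area gives 1.5 × 250 = 375 cases. The half-width for a difference in means is 1.96 × √(867.1²/n₁ + 539²/375).
- Current rate, n₁ = 1.5 × 88 = 132: 1.96 × √(5695.9 + 774.7) = ±158 days
- +60 a year, n₁ = 222: 1.96 × √(3386.8 + 774.7) = ±126 days

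With means of 293 and 264 against medians of 38 and 58, the data are strongly skewed, so this normal approximation is rough.

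**The case against.** The article never says that Table 3 was built from Table 2. It refers to historical DUP data for both areas without printing their mean or SD, and 308 and 585 could come from there. Table 2 is also not a clean planning source: it covers August 2011 to August 2012, while the campaign launched in January 2012. This stands. The two inputs can be called unsupported and inconsistent with Table 2, but not wrong, and figures computed from 867.1 and 88 are illustrations rather than corrected values. It does not rescue the sample size: the column is called an increase and used as a total, whatever the source of the mean and SD.

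A reader might infer that the table overstates precision, because putting 867.1 in place of 585 at the same n widens every interval. The documents do not support that as a conclusion. It corrects the SD while keeping the n that is itself the error. With baseline cases restored over 18 months, the half-widths are narrower than printed in every row.

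Table 3 is openly captioned for the target area, so the missing contrast is not an arithmetic error, and further detail may sit in a fuller document. That also stands. The contrast is worth adding because it is the key outcome, but the fault lies in the table as printed.

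Finally, the trial takes all new cases accepted by the service, and no sample size or decision rule depends on Table 3. That limits the severity.

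**Conclusion.** Table 3 is wrong as labelled. That eight rows share one centre and fit one SD, with n equal to the stated increase, leaves little doubt about how it was built, given 95% t intervals. Restoring the 88 baseline cases changes the bold row from ±151 to about ±95 (12 months) or ±77 (18 months) at the table's own SD, and to ±141 or ±115 at Table 2's SD. If the column is really a total, the labels are wrong instead, and six of the eight rows describe fewer cases than were already observed.

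The mean of 308 and SD of about 585 are unsourced. The omitted baseline cases widen the printed intervals and the SD below Table 2's narrows them, so no single statement that precision is over- or understated is justified. The recomputed figures rest on 88 cases a year, a period that overlaps the campaign, and on normal-theory intervals for skewed data. This should be fixed; the conduct of the trial does not depend on it.

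**What to change.** 1. State the source of the mean and SD behind Table 3, and the confidence level, and reconcile the inputs with Table 2. If they come from the historical data, print those figures.
2. Recompute with n = 1.5 × (baseline yearly cases + increase) for the 18-month window, preferably with a baseline rate from before the January 2012 launch. If the first column was meant as total yearly cases, rename it, correct the caption and lead-in, and choose rows consistent with the observed rate.
3. Relabel the third column: it holds confidence limits, not widths.
4. Add the expected confidence interval for the between-area contrast that will serve as the effect size, on the scale on which it will be analysed. The ±158 and ±126 days above only indicate the order of magnitude.

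The cost is one recalculated table and a sentence on its inputs. Recruitment, data collection and intervention are unaffected.

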### Secondary analysis

#### Website visits

We also predict there will be an increased number of online visits to our website http://www.youthspace.me/psychosis. The website went live in September 2011. Website visits will be monitored on a monthly basis before, during and after the intervention.

#### UK benchmark DUP data

The trial benefits from extensive DUP data from UK National EDEN sites in Cambridge, Cornwall, Blackburn, Blackpool, Burnley, Lancaster and Norwich [18].

## Discussion

Although reducing DUP is a UK Department of Health target, there has been no effective strategy for achieving this in the UK. This is the first UK trial attempting to reduce DUP. The ethnic profile of Birmingham, however, is diverse and includes large numbers of inhabitants of Asian and Black heritage, therefore, any findings from this intervention, will be need to be carefully considered in light of this diversity. Our application of the Precede/Proceed public health model in the design and implementation of the trial, nonetheless, will provide a *generalizable* methodology that should be applicable to a variety of healthcare contexts with differing sources of delay.
